### Sample size

A minimally important difference (MID) for change in AFEQT score was not identified in a review of the literature. In the initial validation study [37], the SD for change from baseline to 3 months in the medically managed group was 20.0 (overall AFEQT global score). This group is most like the projected population for this study, and that value was therefore used as the SD for sample size calculations. We consulted [name], an experienced arrhythmia specialist, AF QoL researcher, and coauthor of the AFEQT questionnaire, who suggested that the MID for AFEQT is 12. As such, we chose an effect size of 12 (i.e., NP-led care would improve AFEQT scores by at least 12). A sample size of 64 participants in each group will detect an MID of 12 in AFEQT scores (SD 20, two-tailed *t* test, 80% power, and significance level of 5%). Seventy patients per group (total 140) will be recruited to allow for 10% loss to follow-up.

All sociodemographic and clinical characteristics for the intervention (NP-led care) and control groups at baseline will be summarized using mean ± SD for continuous variables and the observed counts and percentages for categorical variables. For the main outcome, analysis of covariance (ANCOVA) will be used to assess change in AFEQT scores over time: baseline to 3 months and 3 months to 6 months (repeated dependent measures) in both the intervention and control groups. ANCOVA assumes normal distribution of the data as well as homogeneity of variance and the groups being balanced. Adjustment for pretest scores will identify whether the postintervention difference in scores is truly a result of the intervention. ANCOVA will also account for variation around the posttest means that comes from the variation attributed to the patients AFEQT scores started at baseline. Previously, it has been shown with other HRQoL scores that data can be skewed because of ceiling or floor effects resulting from extreme values and unequal distances between values on ordinal scales [40]. However, the central limit theorem states that the means will be normally distributed regardless of the original distribution when there are at least 30 per group [41]. This study is projected to have 2 equal groups with 70 participants. If the initial data analysis reveals nonnormal distributions and skewed data, further analysis will be completed to determine if transformation of the data is required or if other statistical analysis would be more appropriate. An independent *t* test will be used to assess the difference in means between NP care and physician-led care. Kaplan-Meier survival analysis will be used to evaluate the composite endpoint of cardiovascular death and hospitalizations determined by blinded assessors. Multivariate analysis will be used to adjust for possible differences in baseline characteristics and scores for any significant variables. Consultant satisfaction will be determined by comparing the means with independent *t* tests. A *p* value less than 0.05 will be considered statistically significant. All analyses will be based on the intention-to-treat principle.

Missing data will be replaced with the overall mean of the missing variable. This technique is known to accurately identify the mean but will underestimate the SD, making the CI overly optimistic [42]; however, other options also have imperfections. This will need to be considered in the final analysis. All analyses will be performed with the latest version of IBM SPSS statistical software (IBM, Armonk, NY, USA).

Data entry will be completed in a mature, secure web application specifically developed for surveys and databases. An application has been specifically designed for this study with limits built into data entry fields to limit errors. Data entry will be completed by [name] with random data entry checks done by a specific Epidemiology Coordinating and Research (EPICORE) Centre staff member. The final dataset will be available only to [name] and a specific EPICORE Centre staff member. We did not feel that a data monitoring committee was needed for the following reasons. First, the NP intervention is already part of how care is delivered at our institution. We are simply evaluating it. Second, because this is a trial of a treatment approach, we did not feel that data monitoring would be necessary (and our research ethics board did not require it).

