**Methods/design:**

We plan a randomized controlled trial comparing NP-led care vs. standard care. Inclusion criteria are ≥18 years of age, documented nonvalvular AF, willingness to give informed consent, and capacity to complete questionnaires. Patients referred for electrophysiological intervention who are clinically unstable or unable to attend follow-up visits will not be eligible to participate. Patients will be asked for verbal consent during the initial triage phone call from the nurse. Randomization will occur via a secure website. The intervention includes an NP consult, including medical history, physical examination, patient teaching, treatment plan, and follow-up at 3 and 6 months. The control arm involves usual cardiologist consultation with follow-up determined by the cardiologist’s practice pattern. The primary outcome will be the difference in change in Atrial Fibrillation Effect on Quality of Life Survey scores at 6 months between groups. Secondary outcomes will include difference in change of EQ-5D scores at 6 months between groups, difference in composite outcomes of death resulting from cardiovascular cause, hospitalizations and emergency department visits between groups, and satisfaction with NP-led care measured by the Consultant Satisfaction Questionnaire. A sample size of 70 per group will ensure adequate power despite a potential 10% loss to follow-up.

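### The sample size does not follow from its stated inputs: 12 points, SD 20 and 80% power need 45 per group, not 64

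*Protocol article*

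**What the plan says.** The Sample size section of the protocol article gives every input to the calculation.

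- **Target difference:** "we chose an effect size of 12 (i.e., NP-led care would improve AFEQT scores by at least 12" points. The section reports that no minimally important difference was found in the literature and that the value came from a consulted expert.
- **SD:** taken from the questionnaire's validation study, where "the SD for change from baseline to 3 months in the medically managed group was 20.0 (overall AFEQT global score"). The section says that this value was used in the calculation.
- **Test, power and alpha:** "SD 20, two-tailed *t* test, 80% power, and significance level of 5"%.
- **Result:** "A sample size of 64 participants in each group will detect an MID of 12 in AFEQT scores".
- **Allowance for loss:** "Seventy patients per group (total 140) will be recruited to allow for 10% loss to follow-up".

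The Design and setting section specifies two equal groups and a superiority comparison. The abstract (Methods/design) repeats the conclusion: "A sample size of 70 per group will ensure adequate power despite a potential 10% loss to follow-up".

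**The concern.** Sixty-four per group is the familiar two-sample t-test answer for a standardized difference of 0.5 at 80% power and two-sided 5%. The stated inputs give a standardized difference of 0.6, which needs far fewer patients. Difference, SD, power, alpha and sample size therefore cannot all be right.

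This matters because the paragraph tells readers what the trial was built to detect. It will probably be carried into the results paper and used to interpret a null result. If the calculation really used 10 points, the reported target is wrong. If it used an SD near 24, the SD attributed to the validation study is wrong. If 12, 20 and 80% are all correct, the document gives no reason for a substantial share of the 140 patients. The target difference needs the most clarity, because it rests on one expert's opinion and not on published evidence.

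**Working it through.** **Inputs** (Sample size section, with equal allocation from Design and setting): difference δ = 12, SD σ = 20, two-sided α = 0.05, power 0.80, ratio 1:1.

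**Step 1. Required size from the stated inputs**

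Normal approximation: n per group = 2 (z₀.₉₇₅ + z₀.₈₀)² (σ/δ)²

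- (1.960 + 0.842)² = 7.849
- (20/12)² = 2.778
- n = 2 × 7.849 × 2.778 = 43.6, so 44 per group

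The exact noncentral t calculation, which matches the stated test, gives 44.6, so **45 per group**. The stated 64 is 64/45 = 1.42 times this.

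**Step 2. Can 64 be reproduced?**

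| Variant (12 points, SD 20 unless noted) | n per group |
|---|---|
| One-sided 5% | 35 (normal) |
| α = 0.025, for two time points | 53 (normal), 55 (t) |
| 90% power | 59 (normal), 60 (t) |
| 95% power | 73 (normal), 74 (t) |
| α = 0.01 | 65 (normal), 67 (t) |
| Inflation for a rank test | 47 to 52 |
| **10 points, SD 20 (d = 0.5)** | **63.8, so 64 (t)** |
| **12 points, SD about 24.0 (d = 0.5)** | **64 (t)** |
| **12 points, SD 20, power about 92%** | **64 (t)** |

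Reading 64 as a total also fails, since the requirement is then 2 × 45 = 90. An α of 0.01 comes near 64 but contradicts the stated 5%. The paragraph mentions no allowance for multiplicity, clustering or non-normality, and loss to follow-up is applied only after 64. The planned baseline-adjusted ANCOVA would lower the requirement, not raise it.

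**Step 3. Power that the stated sizes give (SD 20, two-sided 5%)**

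The noncentrality parameter is (δ/σ)√(n/2). For 64 per group it is 0.6 × √32 = 3.39 at 12 points and 0.5 × √32 = 2.83 at 10 points.

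| Evaluable per group | Power, 12 points | Power, 10 points |
|---|---|---|
| 64 | 92.0% | 80.1% |
| 63 | 91.6% | 79.5% |

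With 64 per group and 80% power, the detectable difference at SD 20 is 9.98 points.

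**Step 4. Allowance for loss**

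- 70 × 0.90 = 63, one short of 64.
- 64 / 0.90 = 71.1, so 72 would have to be recruited.
- 70 can lose 6 before falling below 64: 6/70 = 8.6%.
- If the requirement is 45, then 45 / 0.90 = 50 per group, or 100 in total, 40 fewer than planned.

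**The case against.** The best defence is that the error is harmless. If 64 is read as a sufficient number, it does provide at least 80% power for 12 points at SD 20. Understating power is conservative, and neither design, analysis nor enrolment has to change. All of that is true. It limits the consequence but does not make the figure correct: the paragraph presents 64 as the result of five inputs that give 45.

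A second objection is that the documents cannot show which number is wrong. The difference, the SD, the power or the 64 itself could be at fault. If an SD of about 24 was used, the printed 80% for 12 points would be right and the 92% figure would not apply. This stands, and it determines the order of the correction: find the source first, then restate. An SD of 24 is less likely than a 10-point difference, because the section says explicitly that 20.0 was used.

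Third, the shortfall after loss is trivial. The usual shortcut, 64 × 1.10 = 70.4, explains the 70, and moving from 64 to 63 costs 0.4 percentage points of power at 12 points and 0.6 at 10. It is a slip of one patient per group and irrelevant if 45 is the true requirement. Likewise, the abstract's sentence about adequate power is not false on the stated inputs, since 63 evaluable per group gives 91.6%. It needs only to agree with the corrected paragraph.

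**Conclusion.** The concern holds. On the stated inputs the requirement is 45 per group, and the stated 64 exceeds it by 19 patients (42%). No adjustment described in the document closes the gap. Taking SD 20 as given, the trial has about 92% power for 12 points, or about 80% for 10, and not 80% for 12.

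These powers assume an unadjusted two-sample t test, equal groups and the stated SD. The most natural explanation is a calculation at a standardized difference of 0.5, but the document cannot confirm it. The error is in the safe direction. It is still a mistake in the sample size justification for the primary outcome and should be corrected before the results are reported. The loss calculation is a minor slip in the same paragraph.

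**What to change.** 1. Retrieve the original calculation and establish which difference, SD and power were entered.
2. If SD 20 was used, keep 140 and replace the last part of the Sample size section with text such as: *With 70 recruited and 63 evaluable per group after 10% loss, an SD of 20 and a two-sided 5% t test, the trial has about 92% power for a 12-point difference and about 80% power for a 10-point difference.*
3. If the calculation used a 10-point difference, or an SD of about 24, state that value and its source, and give the power that follows from it.
4. State the loss allowance in terms of the 63 per group that remain, and bring the abstract sentence into line.

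The cost is a wording change in one paragraph and one abstract sentence. Enrolment and analysis are unaffected. The Trial status section reports 31 patients enrolled, so at that stage the correction could be made well before analysis.

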### Outcomes

The primary outcome is the difference in change in AFEQT scores from baseline to 3 months and 6 months between the intervention and control groups. AFEQT is an AF-specific questionnaire [37] for use with patients with any type of AF. AFEQT is a simple survey with 20 questions based on a 7-point Likert scale covering 3 domains. The questionnaire should take about 5 minutes to complete. Four questions assess AF-related symptoms, eight questions evaluate daily functioning, and six questions evaluate AF treatment concerns. Two questions assessing satisfaction with treatment are not included in the overall score. Questions 1–18 are included in the overall scoring of the questionnaire. A score of zero corresponds to complete disability, whereas a score of 100 corresponds to no disability. The AFEQT has been shown to have good reliability, test-retest reliability, construct validity, and responsiveness as well as discriminatory properties between clinically different groups [37]. The lowest global score is associated with the patients with severe symptoms related to AF. The AFEQT has also been shown to be responsive to change [37].

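### The main-outcome ANCOVA is set on baseline-to-3-month and 3-to-6-month change, does not name the baseline-to-6-month contrast, and so leaves open which comparison decides the trial

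*Protocol article*

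**What the plan says.** The protocol article describes the primary comparison in three places, and they differ.

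- **Abstract, Methods/design:** "The primary outcome will be the difference in change in Atrial Fibrillation Effect on Quality of Life Survey scores at 6 months between groups". This is one time point, 6 months.
- **Outcomes:** "The primary outcome is the difference in change in AFEQT scores from baseline to 3 months and 6 months". These are two time points, both measured from baseline.
- **Analysis text under Sample size:** for the main outcome, ANCOVA will "assess change in AFEQT scores over time: baseline to 3 months and 3 months to 6 months". These are two successive intervals, and the second starts at 3 months.

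The analysis text also describes the covariate. It says "Adjustment for pretest scores will identify whether the postintervention difference in scores is truly a result of the intervention", and that the model accounts for "variation around the posttest means that comes from the variation attributed to the patients AFEQT scores started at baseline". Both statements point to the baseline AFEQT score. Later in the same paragraph it adds: "An independent *t* test will be used to assess the difference in means between NP care and physician-led care". No outcome or visit is attached to that test. Satisfaction has its own t test sentence further on.

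**The concern.** The 3-to-6-month interval starts from a score that treatment may already have changed. A between-group difference in that interval measures further divergence after 3 months. It does not measure the effect at 6 months. The effect named in the abstract is the sum of the two interval effects, and a test of each part is not a test of the sum.

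Three candidates could therefore be reported as the primary result: the first interval, the second interval, and an independent t test at an unstated time. No rule chooses among them. They agree only for some courses of benefit over time. If the benefit builds slowly or fades, the choice of contrast decides whether the trial is called positive.

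**Working it through.** **Inputs from the protocol article (Sample size).** The target difference is 12 AFEQT points. The SD is 20, given as the SD of change from baseline to 3 months. The test is two-sided at 5%, with 64 per group before allowance for loss.

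**Assumptions, not in the document.** The SD of change is 20 over every interval. Variance is equal at all visits, and the correlation ρ between any two visits is 0.3, 0.5 or 0.7.

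**The plan's own figure.** A 12-point difference with SD 20, 80% power and two-sided 5% needs 44 per group (normal formula) or 45 (exact t test), so the stated 64 is not reproduced. At 64 per group an unadjusted t test on change has about 92% power. That is a separate matter. Here 64 serves only as the planned number per arm.

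**Step 1: expected effects.** Let e3 and e6 be the true between-group differences at 3 and 6 months. Randomization makes the expected baseline difference zero. The expected contrasts are then:

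- baseline to 3 months: e3
- 3 to 6 months: e6 − e3
- baseline to 6 months: e6

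| True course | Baseline to 3 | 3 to 6 | Baseline to 6 |
|---|---|---|---|
| Sustained (12, 12) | 12 | 0 | 12 |
| Gradual (6, 12) | 6 | 6 | 12 |
| Lost (12, 0) | 12 | −12 | 0 |

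Adjusting for baseline does not alter these expectations, and the table needs no assumption about SD or correlation.

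**Step 2: standard errors with 64 per arm.** With change SD 20, the score SD is 20/√(2(1−ρ)). The residual SD of a baseline-adjusted comparison at either visit is that value times √(1−ρ²), which simplifies to 20·√((1+ρ)/2).

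- ρ = 0.3: residual SD 16.1; SE = 16.1·√(2/64) = 2.85
- ρ = 0.5: residual SD 17.3; SE = 3.06
- ρ = 0.7: residual SD 18.4; SE = 3.26

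Under equal correlations the 3-to-6-month change is uncorrelated with baseline, so adjustment gains nothing: SE = 20·√(2/64) = 3.54.

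**Step 3: power.** Approximate power is Φ(effect/SE − 1.96).

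- 12 points, baseline-adjusted at 6 months: ratios 4.21, 3.92 and 3.68, giving about 99%, 97% and 96%.
- 6 points in the first interval: ratios 2.10, 1.96 and 1.84, giving about 56%, 50% and 45%.
- 6 points in the second interval: ratio 1.70, giving about 40%.

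Simulation (3,000 trials per setting, 64 per arm, t reference) gave the following ranges over ρ = 0.3 to 0.7:

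| True course | Baseline to 3, adjusted | 3 to 6, unadjusted or adjusted | Baseline to 6, adjusted |
|---|---|---|---|
| Sustained | 96-98% | about 5% | 95-99% |
| Gradual | 44-53% | 37-39% | 95-99% |
| Lost | 96-99% | 91-92% (in favour of control) | about 5% |

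The formula and the simulation agree to within about 2 to 3 percentage points, as expected from a normal approximation and simulation error.

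**The case against.** The strongest reply is that the 6-month effect is within reach of the plan. The analysis text speaks of repeated measures, posttest means and adjustment for baseline, which fits a baseline-adjusted repeated-measures model. Such a model can yield the 6-month effect as the sum of the two interval effects. The independent t test may also be the 6-month AFEQT comparison, since satisfaction has its own t test and the sample size rests on a two-tailed t test. This stands. A reader might infer that the plan never estimates or tests the 6-month effect, and the document does not support that reading. What it shows is that the 6-month contrast is not named. If the t test is the 6-month comparison, it is an unadjusted analysis standing beside the ANCOVA assigned to the main outcome, and the text does not say which governs.

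A second reply is that under a sustained benefit the first interval shows the 12 points, and a null from 3 to 6 months correctly reports no further change. This also stands. The benefit would be missed only if the second interval were read as the primary result, which the text does not say. The gradual and lost courses do not depend on that reading.

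Two other inferences should be resisted. One is that the 3-month score will be the covariate for the second interval, so that the model conditions on part of the treatment effect. The text ties adjustment to scores at baseline and does not propose this. The other is that the trial was sized for 6 months. The SD used is for 3-month change, and no time point is given for the 12-point difference.

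**Conclusion.** The point holds as an unfixed primary contrast. The analysis text names two successive intervals, the abstract names 6 months, and Outcomes names 3 and 6 months from baseline. No single analysis instruction satisfies all three as written.

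That a sustained benefit gives an expected 3-to-6-month difference of zero is arithmetic and needs no assumption. For a gradual benefit, neither listed interval has much more than an even chance of significance, while the 6-month comparison is nearly certain to detect it. For a benefit lost by 6 months, the first interval would nearly always be significant although the 6-month effect is zero. The power figures rest on a change SD of 20 at every interval, equal correlations of 0.3 to 0.7, 64 analysed per arm and the three assumed courses. Other values would move the percentages but not the mismatch.

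The contrast decides the trial's conclusion, so it should be settled before outcomes are analysed.

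**What to change.** In the analysis text, replace the two-interval statement with wording such as: *The primary analysis is the between-group difference in AFEQT score at 6 months, adjusted for baseline AFEQT, estimated from a repeated-measures model with the 3- and 6-month scores as outcomes and with arm-by-visit and baseline-by-visit terms. The baseline-adjusted difference at 3 months is secondary. Change from 3 to 6 months is descriptive.*

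State which outcome and visit the independent t test applies to, or remove it for AFEQT. Align the abstract and Outcomes so that both name 6 months as the single primary time point.

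The cost is wording only. Visits, questionnaires and data stay the same. Trial status reports 31 patients enrolled, against the 140 planned, so the change could be made well before the final analysis.

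### Overall-mean imputation of missing outcome scores distorts the between-arm AFEQT difference: at the planned 10% loss, if unrelated to outcome, a true 12 becomes about 10.8

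*Protocol article*

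**What the plan says.** The rule stands near the end of the analysis text that follows the Sample size heading of the protocol article: "Missing data will be replaced with the overall mean of the missing variable". It covers all variables, exempts no outcome, and is the only missing-data rule given. The article then assesses it: "This technique is known to accurately identify the mean but will underestimate the SD, making the CI overly optimistic". It adds that the alternatives have flaws too and that the matter must be borne in mind at the final analysis. It names no alternative method and no sensitivity analysis.

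Under Outcomes, the primary outcome is a contrast between the arms in AFEQT change from baseline to 3 and 6 months. The analysis is ANCOVA with adjustment for the baseline score (an independent t test is also named), by intention to treat. On loss, the Sample size section says: "Seventy patients per group (total 140) will be recruited to allow for 10% loss to follow-up".

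**The concern.** The defence of the rule concerns the wrong quantity. Filling gaps with the overall mean leaves the overall mean where it was. The trial, however, estimates a difference between two arm means. Each missing patient, in either arm, receives a value that lies between the arms, so each arm is drawn toward the other. The filled value also ignores the patient's own baseline and 3-month scores, although the planned ANCOVA relies on the baseline score to predict the outcome.

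At stake are the primary estimate and its confidence interval. The article concedes part of the problem with the interval. It does not recognise that the difference itself is biased. Because the rule is stated in the protocol, this is not a detail left to a later analysis plan.

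**Working it through.** **Inputs from the article (Sample size).** Difference 12 ("we chose an effect size of 12"); SD 20 ("the SD for change from baseline to 3 months in the medically managed group was 20.0"); two-sided 5% level; 70 per arm; 10% loss.

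**Assumptions made here.** Whole outcome scores are missing. For ANCOVA, the baseline SD is 20 and the correlation between baseline and 6 months is 0.5, which gives an SD of change of √(400 + 400 − 2 × 0.5 × 400) = 20. Every loss rate other than 10%, and every mechanism of loss, is assumed.

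**1. The plan's own figure.** n = 2 × (1.960 + 0.842)² × (20/12)² = 43.6, so 44 per arm (45 by the t distribution). The stated 64 is not reproduced; it matches a difference of 10 (63.8). That is a separate matter, and nothing below uses 64.

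**2. Size of the shrinkage, loss unrelated to outcome.** Let A and B be the observed arm means and M the overall observed mean. With fraction m missing in each arm, the filled arm means are (1 − m)A + mM and (1 − m)B + mM. Their difference is (1 − m)(A − B).
- 10%: 0.9 × 12 = 10.8
- 20%: 0.8 × 12 = 9.6
- 30%: 0.7 × 12 = 8.4

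**3. Standard error and coverage at 10%.** The model SE after filling is about 20 × √0.9 × √(2/70) = 3.21. The simulated SE from observed scores is 3.55, so the interval is about 10% narrower. It is also off-centre by 1.2/3.21 = 0.37 SE. Coverage is then about Φ(1.98 + 0.37) − Φ(−1.98 + 0.37), or 94%. Simulation (70 per arm, true difference 12; 20,000 runs for the t test, 6,000 for ANCOVA) agrees. Cells show estimate (SE), coverage:

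| Loss per arm | t test, filled | t test, observed | ANCOVA, filled | ANCOVA, observed |
|---|---|---|---|---|
| 10% | 10.8 (3.21), 93.7% | 12.0 (3.55), 95.3% | 10.8 (2.84), 92.9% | 12.0 (3.09), 94.7% |
| 20% | 9.6 (3.04), 87.9% | 12.0 (3.77), 95.1% | 9.6 (2.74), 87.0% | 12.0 (3.28), 95.0% |
| 30% | 8.4 (2.85), 75.8% | 12.0 (4.03), 95.2% | 8.4 (2.61), 72.0% | 12.0 (3.51), 95.0% |

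Estimate and SE shrink nearly together (10.8/3.21 = 3.36; 12.0/3.55 = 3.38), so power at 10% loss is 92.1% either way for the t test, and 96.8% against 97.2% for ANCOVA. With no true effect, rejection stays at about 5%.

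**4. Unequal loss, unrelated to outcome.** With o₁ and o₀ patients observed out of n per arm, the factor is 2o₁o₀/[n(o₁ + o₀)]. For about 5% and 25% loss (4 and 18 of 70 missing): 2 × 66 × 52/(70 × 118) = 0.831, and 12 × 0.831 = 9.97. Simulation gives 9.98, coverage 90.3%. Under the null, rejection is 4.8%, and with 5% versus 30% loss in ANCOVA it is 4.5–4.7%. Unequal loss alone does not inflate type I error.

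**5. Loss that differs by arm and depends on baseline.** The assumed case is 5% loss in the NP arm and 30% in control, with low-baseline patients missing more often. Control patients who would have scored low receive an average value, and the ANCOVA cannot undo this. With no true effect, the bias is about −2 points and type I error about 10–12%, against 5.1% from observed scores. With a true 12, the estimate is 7.7–7.9 and coverage 67–69%. Milder assumed cases give type I error of 7.4% (5% versus 20%) and 6.4% (5% versus 15%).

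**6. Loss that depends on outcome in one arm.** Take 10% loss in each arm and a true 12.
- NP-arm dropouts 20 points worse than NP completers: the observed difference is 12 + 0.1 × 20 = 14, and after filling 0.9 × 14 = 12.6, above the truth.
- The same in control: observed 12 − 2 = 10, and after filling 9.0.

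**The case against.** Much can be said for leaving the rule alone, and several points stand.

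- **Disclosure.** The article already concedes the too-narrow interval and says it must be considered. Only the bias in the difference is new.
- **Modest size at the planned loss.** At 10% the shrinkage is 1.2 points, coverage falls by about two percentage points, and power barely moves. The worse figures need 20–30% loss in an arm, which the article nowhere projects; under Study population it provides telephone reminders at 2 and 4 weeks.
- **Unclear level.** The rule does not say whether items, visit scores or change scores are filled. If gaps are mostly single items among the 18 scored, the effect on the total is far smaller. If visit scores are filled and raw change is compared, the difference still shrinks to 10.8 but the SE is about 3.39, so the interval narrows less.

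Three stronger readings are tempting, and the document does not support them.

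- **That the bias always runs toward zero.** Step 6 shows a case above the truth, and step 5 moves away from zero under the null.
- **That mailed control questionnaires inflate type I error.** Mailing applies to any patient not seen in follow-up. Because the NP arm has scheduled visits at 3 and 6 months, higher control non-response is plausible, but no rate is given. Inflation also needs loss to depend on prognosis, and in the case examined the error ran against NP care.
- **That giving the dead an average score matters materially.** The article projects no death rate for this 6-month trial. Its only figures, 1.1% and 3.9% cardiovascular deaths, come from a cited 2-year trial.

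**Conclusion.** The point holds in a limited form. The statement that the method recovers the mean does not carry over to the between-arm difference. Under the mechanism most favourable to the rule, with loss unrelated to outcome and whole scores missing, the primary estimate is attenuated by the missing fraction: 12 becomes about 10.8 at the article's own 10% loss, with about 93% coverage under the assumed correlation of 0.5. At that rate neither power nor the level of the test is meaningfully harmed; the damage is to the estimate and its interval.

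Outside that mechanism the direction of bias is not predictable, and type I error is at risk only when loss both differs by arm and depends on prognosis or outcome. Where loss was unrelated to outcome, or depended only on baseline, baseline-adjusted analysis of observed scores was unbiased with about 95% coverage, so the rule did worse than not imputing at all. An admitted defect in the interval with no correction attached, together with an unrecognised bias in the estimate, justifies changing the rule.

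**What to change.** Withdraw overall-mean imputation for outcome scores and delete the claim that it identifies the mean accurately. In its place, analyse the observed 3- and 6-month AFEQT scores adjusted for baseline, preferably in a likelihood-based repeated-measures model, which uses every observed visit. Multiple imputation by arm, including the baseline and 3-month scores, is an acceptable alternative. State the level at which the rule applies (item, visit score or change). Mean imputation may stay for missing baseline covariates.

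Neither replacement cures loss that depends on the unobserved outcome: in step 6 the observed-score difference is itself off by 2 points in either direction. A sensitivity analysis that shifts imputed values by arm, and separate reporting of deaths, would be useful but optional.

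The cost is analysis wording. No new data or patients are needed, and the repeated-measures model is available in the SPSS software already named. The article reports 31 of 140 patients enrolled, so at that stage the change could precede any outcome analysis. The downside is a slightly wider interval: at 10% loss, an ANCOVA SE of 3.09 instead of 2.84.
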